### Data collection during the study period

The intervention period for each woman is approximately 37 months (~ 7 months pregnancy and the first 30 months of the child’s life). GPs recruited women consecutively and therefore, the 37 months intervention period did not start simultaneously for all included patients. Maternally-reported data (Table 2) are regularly collected from inclusion to the end of the study. Thus, most participant data will be collected at three time-points:Inclusion (baseline)When the child is 15 months andWhen the child is 30 months

The baseline demographic questionnaire included educational qualification level, employment status, and household composition. All data collected from the women are collected through E-boks, a private and secured online digital mailbox that all citizens in Denmark have.^2^ Baseline data for the study will consist of GP-reported data, patient-reported data, and Danish administrative register data. GP-reported data (including the developmental assessment data) and the families’ self-assessments are completed electronically by use of REDCap [60]. Information about services from the social and health care system will be collected through Danish registers.

#### End-of-study data collection

After completion of the approximately 37 months intervention period for each woman, a questionnaire with primary outcomes (CDI and SDQ) will be sent to the women, followed by the remaining questionnaires. Participants will receive 2 automatic reminders and subsequently a text message to ensure the completeness in data. Mothers’ and their children’s service use will be collected from registers. All data are stored in REDCap [60].

#### Statistical methods

Binary valued outcomes will be analysed in logistic regression and continuously valued outcomes will be analysed in linear regression. To account for clustering within practices and for possible repeated measurements, generalised estimating equations (GEE) will be employed to adjust the covariance matrix. Possible differential dropout will be adjusted for using inverse probability weighting [61].

## Process evaluation

The main objectives of the process evaluation are:

○  To identify the key enablers and barriers for signposting the robustbarn.dk programme in clinical practice○  To provide an empirically grounded explanation of the results from the family resilience cluster randomised clinical trial.○  To contribute to the family resilience project’s overall assessment of the value, implications, and potential scalability and transferability of the intervention.

These objectives involve monitoring and exploring how professionals and patients respond to the intervention (with what type of consequences), how the intervention is actually implemented in practice (if it is implemented as intended in the protocol, i.e. implementation fidelity), and how contextual factors influence implementation processes, mechanisms, and outcomes [62].

The implementation process will be evaluated using Normalization Process Theory (NPT), which provides an explanatory framework for investigating how complex interventions are implemented in organisational settings. According to the theory, implementation emerges through four generative mechanisms: coherence, cognitive participation, collective action, and reflexive monitoring [63, 64].

### Process evaluation data collection and analysis

The study will adopt a mixed-methods approach combining in-depth qualitative data with quantitative process data on intervention activities [62].

#### Qualitative interviews and observations

During and after the randomised clinical trial, semi-structured, face-to-face interviews will be conducted with purposively sampled health professionals and patients from 15 practices. The aim is to conduct approximately 20 interviews with health professionals and 20 interviews with their patients. The interviews will be audio-taped and transcribed verbatim. First, the data material will be analysed using an inductive thematic approach, and subsequently, a more deductive thematic analysis will be performed using NPT as a coding framework.

#### Quantitative data

This qualitative study will be supplemented by descriptive quantitative data on key process indicators, preferably from all sites or participants, for example number and duration of interventions website visits. Women’s use of the homepage during the first year after entering the study will be analysed in order to describe how their characteristics are associated with the use of the intervention. Further, data about the general practices will be assessed to examine how different practice characteristics affect the women’s use of the intervention. The following data regarding general practice characteristics will be handled; practice area deprivation, practice organisation categorised as single-handed practice, companionship practice or group practice, practices with or without a nurse or midwife and how many women each practice had recruited.

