**Methods:**

The study is a cluster-randomised controlled trial based in general practices in the Capital Region and the Zealand Region of Denmark. Seventy practices were included. Practices were randomised by a computer algorithm in a ratio of 1:1 to intervention or control groups. Each practice was asked to recruit up to 30 women consecutively at their first scheduled antenatal assessment. Clinicians in both groups received one day of training in preventive antenatal and child development consultations with added focus on parental psychosocial well-being, social support, and parent–child interaction. These preventive consultations delivered in both trial arms require enhanced data recording about psychosocial factors. In intervention clinics, clinicians were asked to signpost a web page at three scheduled antenatal consultations and at four scheduled consultations when the child is 5 weeks, 5 months, 1 and 2 years.

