##### Identification and recruitment of pregnant women

GPs participating in the trial consecutively invited all pregnant women attending their first antenatal assessment, usually in gestation weeks 6–10. Each practice was asked to recruit a minimum of 10 and a maximum of 30 consecutive participants at their first pregnancy assessment starting October 2019. Data were recorded for women who declined participation, and participation rates were monitored carefully.

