##### Robustbarn.dk

GPs and staff participating in the intervention arm were introduced to the background, the structure and the aim of the website *robustbarn.dk.* Furthermore, they were trained in presenting the intervention to the parents at each preventive examination and in other consultations where the GP considered it likely that the programme could be useful to the family e.g. when they reported mental difficulties during pregnancy or postnatally. All pregnant women in the intervention arm were introduced to the webpage by their GP at the first antenatal appointment. Women also received a leaflet, with a brief description of the website content. Once the GP included a pregnant woman into the project, the woman received a unique login to robustbarn.dk in her safe electronic mailbox (Eboks). This procedure ensured that only women in the intervention group could access the website and thereby should prevent contamination across study arms.

Robustbarn.dk is a website specifically designed for pregnant women and new parents. The content is based on the module-based generic training programme “The resilience programme” [Danish: robusthedsprogrammet] [42].The programme is based on information about mentalisation, cognitive skills, infant and child neurological development and the function of the nervous system, especially during stress or adversity.

The robustbarn.dk website is a collection of brief psycho-educational texts, sound-files, and exercises (please see supplementary material for more information). The intervention includes e-learning modules to parents related to the timing of antenatal and postnatal consultations e.g. information about normal emotional reactions in pregnancy, preparing for delivery, support in relating to the newborn child etc.

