**Assessments:**				
**ACEs** (Adverse Childhood Experiences)	X			
**CSRQ** (Copenhagen Social Relations Questionnaire)	X			
**ECR-Short Form** (Experience in Close Relationship Scale)	X			
**P-PRFQ** (Prenatal Parental Reflective Functioning Scale)	X			
**Demographic measures** (Questionnaire, Questionnaire 2)			X	X
**EQ-5D-5L** (EuroQol, Quality of Life)	X	X	X	X
**HADS** (Hospital Anxiety and Depression Score)	X	X	X	X
**RLEQ** (Recent Life Events Questionnaire)	X	X	X	X
**Use of robustbarn.dk**	X	X	X	X
**ESSENCE-Q-DANISH** (Early Symptomatic Syndromes Eliciting Neurodevelopmental Clinical Examinations Questionnaire)		X	X	X
**FAD** (The McMaster Family Assessment Device)		X	X	X
**FSS** (Family Support Scale)		X	X	X
**PRFQ** (Parental Reflective Functioning Questionnaire)		X	X	X
**CDI-Short Form** (Communicative Development Inventory at 30 months)				X
**SDQ-Dan** (Strength and Difficulties Questionnaire Danish)				X

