Apart from changes in the child and maternal outcomes, there are likely to be wider benefits. These might include work-related or educational benefits for the affected mothers and their families, increased family cohesion, potential reduction of inequalities between socioeconomic groups, as well as better educational outcomes (eventually) for the children involved. Those benefits may come about as a result of increasing interactions between mothers and their children and other family members, and increased knowledge and skills for continued improved functioning in the future. We shall also collect EQ-5D-5L data from mothers at baseline, every 6 months, and at the end of the trial to capture potential improvement in maternal quality of life.

A sensitivity analysis will be undertaken to explore possible variations of outcome measures and estimate mean effects as well as confidence bands.

As suggested, it is possible that the intervention may lead to long-term benefits to society beyond the trial’s follow-up period. A longer time horizon will provide more time for the effects to accrue and potentially offset the initial costs of the intervention. The long-term benefits of the intervention may include costs saved as a result of conduct and emotional disorders avoided, avoided criminal justice costs, reduced needs for special educational services, reduced mental health service use, and reduced productivity loss for the family as well as improved quality of life for parents. Using longitudinal register data allows for such long-term follow-up.

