### Strengths

The location of this pragmatic cluster-randomised trial in Danish general practice, with its typically high levels of engagement with preventive obstetric and child developmental assessments, is likely to create a robust sample with relatively low levels of attrition assuming patients remain registered with their original GP. Recruitment of consecutive patients attending their first antenatal appointment should provide a sample representing a typical clinical caseload for participating practices. The flexibility given to clinicians in terms of signposting their patients towards the web-based resources should reflect potential future real-world practice underpinned by progressive universalist principles [66] and the quantitative process evaluation of website usage will allow assessment of equity of access to the resources. The strength of Danish population registers will ensure reliable long-term follow-up data for almost all participants.

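### The only stated analysis of website use by women's characteristics covers the first year after entry, about 12 of 37 intervention months, and misses the 1- and 2-year signposting visits

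*Protocol article*

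**What the plan says.** All references are to the protocol article.

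- **Window.** Under Quantitative data (process evaluation), of participating women: "use of the homepage during the first year after entering the study will be analysed in order to describe how their characteristics are associated"; the association meant is with website use. The same paragraph plans descriptive counts and durations of website visits, and an analysis of how practice characteristics affect use. Neither of these carries a time limit.
- **Length of the intervention.** Under Data collection during the study period: "The intervention period for each woman is approximately 37 months", made up of about 7 months of pregnancy and 30 months of the child's life.
- **Entry.** Women are recruited when "attending their first antenatal assessment, usually in gestation weeks 6–10".
- **Signposting.** The abstract's Methods give three antenatal consultations and continue "at four scheduled consultations when the child is 5 weeks, 5 months, 1 and 2 years", which makes seven contacts.
- **Content.** Under Robustbarn.dk: "The intervention includes e-learning modules to parents related to the timing of antenatal and postnatal consultations".
- **Data.** In Table 2 the row "Use of robustbarn.dk" is marked in all four periods, the last two being 15–29 and 30–56 months.
- **Purpose.** Under Strengths, "the quantitative process evaluation of website usage will allow assessment of equity of access to the resources". The Economic evaluation lists "potential reduction of inequalities between socioeconomic groups" among possible wider benefits.

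**The concern.** Whether access is equitable depends on which women use the site, over the whole time it is offered to them. The one analysis that relates use to the woman's own characteristics is tied to a period ending early in infancy, while clinicians go on signposting until the child is 2 and the primary outcomes are measured at 30 months. Modules tied to the later visits would be used after the window has closed.

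At stake is what the trial can say about equity. Early use may be fairly even because every woman in the intervention arm is introduced to the site at her first appointment. If later use drops off mainly among women with less education or fewer resources, the stated analysis would miss it. The unrestricted visit counts could show an overall fall in use, but not who stopped. Practice area deprivation describes the practice and does not stand in for the woman's own circumstances.

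**Working it through.** **Inputs.** Window of 12 months from entry (Quantitative data). About 7 months of pregnancy plus 30 months of child age (Data collection during the study period). Entry in gestational weeks 6–10 (Identification and recruitment of pregnant women). Visits at 5 weeks, 5 months, 1 year and 2 years, after three antenatal visits (abstract, Methods).

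**The plan's own figure.** 7 + 30 = 37 months, as stated.

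**Where the window closes.** Child age at closure = 12 − 7 = 5 months.

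**Coverage.**

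| Period | Inside the window | Outside |
|---|---|---|
| Whole intervention | 12/37 = 32% | 25/37 = 68% |
| Postnatal part | 5/30 = 17% | 25/30 = 83% |

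**Sensitivity to dates.** Assume birth at 39–41 weeks, which the article does not give. With entry at weeks 6–10, the window closes at a child age of 4.0 to 5.3 months and covers 31.5% to 32.7% of the intervention.

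**Visits.**

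- The 1-year visit comes 7 + 12 = 19 months after entry and the 2-year visit 7 + 24 = 31 months after. Entry precedes birth, so both are always more than 12 months after entry, whatever the gestation. That is 2/7 = 29% of contacts.
- The three antenatal visits and the 5-week visit fall inside: 4/7 = 57%.
- The 5-month visit is at the edge. Take 5 months as 21.74 weeks and a year as 52.18 weeks. With entry at gestational week g and birth at week b, the visit is (b − g) + 21.74 weeks after entry. It falls outside when g < b − 30.44. If entry is spread evenly over weeks 6–10 (an assumption), the share outside is (b − 30.44 − 6)/4 = (b − 36.44)/4:

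| Birth week b | Share of 5-month visits after the window |
|---|---|
| 37 | 14% |
| 38 | 39% |
| 39 | 64% |
| 40 | 89% |

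**Recording periods.** Table 2's post-allocation columns are headed per pregnant woman and newborn. Counted from entry, 15 months is later than 12. Counted from birth, 15 months is later than the 5 months at which the window closes. Either way, two of the four periods in which use is marked lie wholly after the window.

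**The case against.** The strongest reply is that nothing here is wrong, only short. The paragraph does not rule out a later analysis by women's characteristics, and a condensed article may leave that to a fuller process-evaluation plan. The window is also defensible as a first look: it takes in the introduction to the site, all antenatal contacts and the 5-week visit, it gives each woman the same length of observation, and the Introduction stresses pregnancy as a formative period. The article also lists exposure to the intervention among the variables collected at 15 months, about 7 + 15 = 22 months after entry, so interest in use does not end at one year. The Strengths section speaks of the usage evaluation as a whole and of access, which could be read as early use.

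Much of this stands as context. The article does not forbid later analysis, the first-year analysis is worth having, and the inequality remark in the Economic evaluation is not tied to website use, so it adds little. But the one-year limit is a stated rule, not a detail left open. The 15-month exposure item comes with no analysis by women's characteristics, and the analyses without a time limit do not use those characteristics. A claim about equity across a 37-month intervention therefore rests, at the level of the individual woman, on its first third. The harm is conditional: the article gives no indication of whether later use is more socially patterned.

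**Conclusion.** The concern holds, as a minor point about the process evaluation. The only stated analysis of website use by women's own characteristics covers about 32% of the intervention, ends at a child age of about 5 months, and always misses two of the seven signposting visits. That conclusion rests on the article's own figures. Only the range for the closing age and the percentages for the 5-month visit depend on assumed birth weeks and, for the percentages, on evenly spread entry; they show no more than that this visit is borderline.

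The comparison of SDQ and CDI between arms and the sample size are not touched. Nothing is lost irreversibly, since use is recorded throughout. The limit is on what could be concluded about equity of access after early infancy.

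**What to change.** Keep the first-year analysis and label it an early report. State that the same analysis will be repeated on use up to 30 months, reported by interval, for example pregnancy, birth to 5 months, 5–15 months and 15–30 months, with the same women's characteristics in each. If this is not done, the equity statement under Strengths should be confined to the first year after entry.

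No new data collection is needed, because Table 2 already marks website use in every period. The cost is some additional descriptive analysis and a later final process report.

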#### Interpretation of qualitative and observational data

Qualitative data will be coded according to the framework of Normalization Process Theory and will address the main objectives described above [65].

## Economic evaluation

The economic cost analysis will consider and present possible costs and benefits associated with the intervention. In particular, the analysis will estimate the costs of the treatment as compared with the costs of the standard care offered to the control group. Furthermore, the economic analysis will assess the benefits of the treatment vis-à-vis standard treatment, e.g. in terms of potential saved short- and long-term costs. To the extent possible, the economic analysis will thus examine the long-term benefits and costs of the intervention.

Costs and benefits will be assessed using linked information from survey respondents to socio-economic and health information in the Danish registers. Linking to register data will facilitates following individuals (parents and children) over time, and the survey will thus be an invaluable source for future follow-up research. The analysis will take a societal perspective to include costs that fall on GPs, other relevant service providers (for example, health visitors or social services) and the affected mothers and their families. Costs of the intervention will be obtained from trial documentation and in consultation with intervention providers. The intervention costs will include GP cost for delivering any relevant components of the intervention, RP staff costs for delivering training, and costs of any consumables required to deliver interventions. Costs of usual care include costs of current care to affected mothers provided by health visitors (sundhedsplejerske) and general practitioners, and also the cost falling on other services (hospital, local authority or other services) through referrals. These data will be combined with study-specific unit costs or unit costs from publicly available standard sources to produce a total cost for both the intervention and control groups.

Apart from changes in the child and maternal outcomes, there are likely to be wider benefits. These might include work-related or educational benefits for the affected mothers and their families, increased family cohesion, potential reduction of inequalities between socioeconomic groups, as well as better educational outcomes (eventually) for the children involved. Those benefits may come about as a result of increasing interactions between mothers and their children and other family members, and increased knowledge and skills for continued improved functioning in the future. We shall also collect EQ-5D-5L data from mothers at baseline, every 6 months, and at the end of the trial to capture potential improvement in maternal quality of life.

A sensitivity analysis will be undertaken to explore possible variations of outcome measures and estimate mean effects as well as confidence bands.

As suggested, it is possible that the intervention may lead to long-term benefits to society beyond the trial’s follow-up period. A longer time horizon will provide more time for the effects to accrue and potentially offset the initial costs of the intervention. The long-term benefits of the intervention may include costs saved as a result of conduct and emotional disorders avoided, avoided criminal justice costs, reduced needs for special educational services, reduced mental health service use, and reduced productivity loss for the family as well as improved quality of life for parents. Using longitudinal register data allows for such long-term follow-up.

## Data management

The study adheres to all Danish laws governing medical research. The General Data Protection Regulation is upheld, and data are stored and handled accordingly. The study owner (University of Copenhagen) is responsible for upholding laws and ensuring the confidentiality of data. All data that can identify participants is encrypted and stored securely on password-protected servers with continuous transaction logging. Trial data are stored in accordance with the data policy of the University of Copenhagen. Data are saved for 5 years after data collection and will thereafter be anonymized or deleted.

### Monitoring

The study has been approved by the University of Copenhagen Data Protection Agency (Case no. 514–0362/19–3000). According to Danish legislation, there is no need to apply for the approval of the National Danish Data Protection Agency when regional approval has been given. A data processing agreement with each GP has been signed before the collection of data. The project management group have met once a month throughout the trial period to monitor recruitment, trial progress, completeness of data and ethical issues. Our Trial steering committee met at the outset of the trial and made a decision to meet on an ad-hoc basis when requested by the investigating team. This has not been required to date, but the TSC will be convened when our final dataset is locked.

